## Abstract

**Background:**

Frozen shoulder is an ailment that denotes dysfunction in the arm characterized by limited range of motion accompanied by pain. The prevalence of adhesive capsulitis is 3% to 5% in the general population and up to 20% in those with diabetes. Physiotherapy, analgesics, corticosteroids, and surgical capsulotomy are common forms of treatment. Administering oil through the nasal route (or *nasya karma*) is mentioned in the Ayurvedic scriptures for managing neck and clavicle disorders. Thermal microcautery (or *agni karma*) is a parasurgical procedure for treating related pathologies of bodily humors (*vata* and *kapha*). This study will aim to compare the efficacy of honey thermal microcautery, standard physiotherapy, and *Sida cordifolia* oil via nasal administration in the treatment of frozen shoulder to determine which provided the most relief.

**Objective:**

The primary aim is to evaluate the efficacy of honey thermal microcautery, standard physiotherapy, and *S cordifolia* oil via nasal administration using the visual analogue scale, range of motion, the Shoulder Pain and Disability Index, and the McGill Pain Questionnaire and compare these interventions. The secondary objective is to assess sustained relief in all 3 groups.

**Methods:**

We will enroll 60 patients, 20 in each group, for this single-blind assessor-controlled study. Group A will receive Ayurvedic treatment, that is, thermal microcautery using honey for 2 days (the first and seventh) and placebo capsules (twice per day) for 7 days, group B will receive standard physiotherapy and placebo capsules (twice per day) for 7 days, and group C will be given *S cordifolia* oil via nasal administration with 8 drops in each nostril and placebo capsules (twice per day) for 7 days. The evaluation parameters are pain (visual analogue scale), range of motion measured using a goniometer, the Shoulder Pain and Disability Index, and the McGill Pain Questionnaire. On September 18, 2023, approval was received from the Institutional Ethics Committee of Mahatma Gandhi Ayurved College Hospital and Research Centre (MGACHRC/IEC/Sep-2023/740).

**Results:**

The results will be subjected to statistical analysis using appropriate methods such as ANOVA. If the ANOVA shows significance, post hoc tests (eg, the Tukey honestly significant difference test) will identify group differences, with *P*<.05 considered significant. As of January 2025, a total of 16 patients have been recruited, divided into 3 groups, and the final results are expected to be published in November 2025.

**Conclusions:**

This comparative study seeks to establish the most effective treatment among honey thermal microcautery, standard physiotherapy, and *S cordifolia* oil *nasya* for managing frozen shoulder, potentially offering new integrative approaches to treating this condition.

## Introduction

### Background

Frozen shoulder (FS) is an ailment frequently seen in general practice. The prevalence of FS, also referred to as adhesive capsulitis and periarthritis, is between 3% and 5% in the general population and up to 20% in those with diabetes. It affects people aged between 40 and 60 years more frequently, including women and manual laborers [1,2]. In patients with diabetes, the incidence is 2 to 4 times higher than in the general population [3]. The prevalence of people who experience pain in the other shoulder after the first shoulder has healed is 6% to 17%, usually within 5 years. It is slightly more likely that the nondominant shoulder will be impacted [4]. The range of motion (ROM) in all directions is significantly reduced in FS (capsular pattern). It results from swelling, scarring, thickening, and shrinking of the capsule that typically encloses the shoulder joint [5]. Global fibroplasia results from a disruption in local collagen translation in FS, which is characterized by severe inflammatory changes in the capsule that point to the involvement of inflammatory mediators (interleukins, cytokines, B and T lymphocytes, growth factors, matrix metalloproteinases, tumor necrosis factors, and fibroblast activation markers) [6-9]. Synovitis-related inflammatory response in the capsule precedes the fibrotic rigidity of the capsule in cases of FS. Using nonsteroidal anti-inflammatory drugs, steroids, physiotherapy, and occasionally hydrodilatation and surgical procedures is the first line of treatment for FS. For most patients, conservative treatment, which includes corticosteroid infiltration and physiotherapy, is considered a suitable choice [1]. Still, despite conservative care, up to 50% of patients claim to have persistent pain, and up to 60% have noticeable motion restriction [10,11].

Steroid injections offer strong anti-inflammatory effects for FS, but potential complications such as pain and glucose changes may prevent patients from accepting this method. Patients endure lengthy rehabilitation times accompanied by a significant degree of pain and everyday disabilities [12,13]. Hence, an alternative Ayurvedic therapy is required in treating FS.

By using Ayurvedic principles, FS can be managed effectively [14] as several studies have investigated the efficacy of Ayurvedic treatments for FS [15]. There are few published clinical studies and case reports on the efficacy of Ayurveda interventions such as *laghumasha tail nasya* [16], *mahamasha taila nasya* [17], *agni karma* with *panchlohashalaka* [18], and *agni karma* with *tamra shalaka* [19].

One study was carried out at the Chaudhary Brahm Prakash Ayurved Charak Sansthan hospital on the efficacy of *mahamasha taila brihana nasya* and *agni karma* and found significant results [20].

### Rationale of the Study

The 3 arms in our study were selected considering their unique mechanisms of action to adequately treat FS. Honey thermal microcautery is an Ayurvedic treatment with thermal effects. Standard physiotherapy is the classic gold standard, ensuring a robust comparator. *Sida cordifolia* oil via nasal route was selected considering its efficacy for *vata-kapha* disorders, particularly musculoskeletal diseases. These treatments were selected considering the evaluation and comparison of diverse approaches between modern medicine and traditional medicine toward optimal outcomes.

No study has been published comparing honey thermal microcautery, standard physiotherapy, and *S cordifolia* oil nasal administration. Additionally, no study has explored the use of honey thermal microcautery in FS. Considering these gaps, this study is essential to determine the most effective and safe therapeutic approach for FS, evaluating interventions such as honey thermal microcautery, standard physiotherapy, and *S cordifolia* oil nasal administration to identify treatments that optimize recovery time and minimize associated concerns.

## Methods

### Overview

This study is an interventional, randomized, single-blind (assessor), 3–parallel arm study to compare the efficacy of honey thermal microcautery versus standard physiotherapy versus *S cordifolia* oil via nasal administration in the management of FS. We will intervene using honey thermal microcautery 2 times (the first and seventh day) along with placebo capsules twice daily for 7 days. Standard physiotherapy will be administered once a day along with placebo capsules twice daily for 7 days. *S cordifolia* oil via nasal administration will be administered via 8 drops in each nostril along with placebo capsules twice daily for 7 days. Follow-up will be conducted on the 8th, 16th, and 32nd days. Placebo capsules will be administered to reduce the psychological effect that patients might feel from knowing that they are not receiving any oral medicine, especially in the honey thermal microcautery group, where the treatment is administered only 2 times a week.

### Objectives

This study aims to determine the comparative effectiveness of honey thermal microcautery, standard physiotherapy, and *S cordifolia* oil nasal administration in managing FS. The primary objectives are to quantify pain reduction, measured via the visual analogue scale (VAS), and assess improvements in ROM, as well as administer the McGill Pain Questionnaire and Shoulder Pain and Disability Index (SPADI) for each treatment group at specific time points: 8 days, 16 days, and 32 days after the intervention.

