#### Primary Variable: Abduction Improvement

The primary variable, shoulder abduction improvement, was used to calculate the minimum sample size required for the study, ensuring adequate power to detect a meaningful difference between groups. The primary variable in this study is shoulder abduction improvement, measured as the increase in the range of motion after the intervention. Based on expected differences, variability, significance level, and power, the minimum sample size required was calculated to ensure reliable detection of a meaningful improvement

Where the mean score for abduction in *shudhabala taila nasya* pre=2.23 (as per the study by Revathi et al [22]).

Mom score for abduction in *shudhabala taila nasya* post at follow-up=1.06.

Difference (pretest-posttest)=1.17

SD=0.58.

Considering 45% superiority in the thermal microcautery group=(1.17) × 45 = 0.526

Mean differenсе *δ*=0.526

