### Statistical Methods

One-way ANOVA will be applied to compare the means of the 3 groups. If ANOVA indicates a significant difference, post hoc tests will be further applied (eg, the Tukey honestly significant difference test) to identify which group differs. A *P* value of <.05 will be considered statistically significant. Covariates such as age and baseline severity will be considered, and adjustments will be made using analysis of covariance if needed. The analysis will be intention to treat, with missing data handled through multiple imputation. Statistical assistance will be provided by a statistician or someone skilled in statistics. We will use SPSS (version 26; IBM Corp) for statistical analysis.

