## Results

Preliminary data collection is ongoing, and participant recruitment for the study commenced in October 2024. As of January 2025, a total of 16 participants have been recruited across all 3 study groups. Data analysis is currently in progress. The final results of the study are expected to be published in November 2025. The study’s findings will be disseminated through peer-reviewed publications.

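### The objectives make four measures at three visits primary while the sample size names abduction alone with no visit, so no single primary test is fixed

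*Protocol article*

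**What the plan says.** The Objective paragraph of the Abstract sets one primary aim: to evaluate the three treatments "using the visual analogue scale, range of motion, the Shoulder Pain and Disability Index, and the McGill Pain Questionnaire and compare these interventions". The Objectives section of the Methods repeats this. It says "The primary objectives are to quantify pain reduction, measured via the visual analogue scale (VAS), and assess improvements in ROM", adds the McGill questionnaire and SPADI in the same sentence, and asks for all four "for each treatment group at specific time points: 8 days, 16 days, and 32 days after the intervention". No measure is ranked above another and no visit is singled out.

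Under Sample Size, the heading Primary Variable: Abduction Improvement gives a different answer: "The primary variable in this study is shoulder abduction improvement, measured as the increase in the range of motion after the intervention". Abduction is one of six shoulder movements in Table 4. No visit is attached to it.

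Statistical Methods plans a one-way ANOVA across the three groups, a Tukey-type post hoc test if the ANOVA is significant, and one criterion: a P "value of <.05 will be considered statistically significant". It does not say to which measure or visit the ANOVA applies.

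The visits are described in two ways. Objectives counts "8 days, 16 days, and 32 days after the intervention". The Methods Overview says "Follow-up will be conducted on the 8th, 16th, and 32nd days", and Table 6 counts study days, with treatment on Days 1 to 7.

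The Results section reports 16 participants recruited and states: "Data analysis is currently in progress".

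**The concern.** Which outcome is primary, and when it is measured, is a matter for the protocol. Here two sections of the same document answer it differently. The trial sets out to name the most effective of three treatments, and the Discussion already expects significant results for honey thermal microcautery. If the deciding test is not fixed, a favourable result on any one measure at any one visit could support that claim at a nominal 5%. Tukey's procedure does not prevent this: it protects the three pairwise arm comparisons within one outcome at one visit, not the choice among outcomes and visits.

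The conflict also affects the sample size. Twenty per group was computed for one variable and one two-group comparison, not for four co-primary measures.

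**Working it through.** **1. The plan's own figure.** Inputs from Primary Variable: Abduction Improvement: pre-treatment score 2.23, follow-up score 1.06, difference 1.17, SD 0.58, and a 45% superiority margin, so δ = 1.17 × 0.45 = 0.526. From Formula Using Mean Difference: 1.96 and 0.84.

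n = 2 × (1.96 + 0.84)² × 0.58² / 0.526² = 19.06, rounded up to 20 per group and 60 in total. This reproduces. With the same inputs, power at 20 per group is 82% for one two-group comparison at 0.05.

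**2. Chance of at least one false-positive ANOVA when the arms do not differ.** For k independent tests at 0.05 this is 1 − 0.95^k. The documents give no correlations between measures or visits, so common correlations of 0.3, 0.5 and 0.7 are assumed and simulated with three groups of 20.

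| Reading of the protocol | Tests | Independent | Correlation 0.3 | 0.5 | 0.7 |
|---|---|---|---|---|---|
| Abduction, one visit | 1 | 5% | – | – | – |
| Abduction, any of three visits | 3 | 1 − 0.95³ = 14% | 13% | 13% | 11% |
| Four measures × three visits | 12 | 1 − 0.95¹² = 46% | 40% | 33% | 24% |

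A second simulation of the 12 tests, with correlations of 0.7 between measures and 0.8 between visits, gives 25%. The 12-test range is thus about 25-40%.

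**3. Cost of keeping several primaries.** Using Bonferroni and assuming that abduction's δ/SD ratio applies to every measure:

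- 12 tests, α = 0.05/12 = 0.0042: 34 per group (102 in total); power at 20 per group is 50%.
- Four measures at one visit, α = 0.05/4 = 0.0125: 28 per group (84 in total); power at 20 per group is 64%.

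**4. Scale of abduction.** The sample size inputs fall from 2.23 to 1.06, so a lower value is better. The section on normal ROM measures each movement by goniometer, and Table 4 gives a normal abduction of 180 degrees. A mean of 2.23 with SD 0.58 cannot be degrees on that scale. It is a graded score, and it also runs opposite to an increase in range of motion. The 20 per group therefore does not, as written, justify a primary endpoint in degrees.

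**5. Time origin.** If treatment ends on Day 7, 8, 16 and 32 days after it would be study Days 15, 23 and 39. The Overview, Table 1 and Table 6 have Days 8, 16 and 32, the first of them one day after the last treatment.

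**The case against.** The strongest reply is that the protocol does name a primary variable, that abduction lies within the ROM listed in the primary objectives, and that broad objectives with one named variable are common. This has force. It would be wrong to say that the powered outcome is not designated primary, because the sample size section designates it. On this reading, though, the visit is still open and the error is about 11-14%. The text also gives no reason to prefer this reading to the Objectives section, which ranks nothing.

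A second reply is that control of multiplicity across outcomes is often left to an analysis plan, and none is shown. That also stands: the absence of an adjustment is not itself the finding. But an analysis plan cannot reconcile two statements in the protocol about what is primary. Statistical Methods does not literally say that each measure at each visit is tested at .05, so the 12-test figure is the consequence of one plain reading, not a stated plan.

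Two stronger readings are tempting and are not supported:

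- A reader might count the six movements separately, giving 27 tests (nine measures × three visits). Nothing in the document says they will be tested separately.
- A reader might infer from the Results section that groups have already been compared, and attach an inflated error rate to an interim look at 16 of 60. The section says that 16 were recruited, not that they completed follow-up, and it does not say that arms were compared or a hypothesis tested. It warrants a clarification, not a number.

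**Conclusion.** The concern holds as a conflict within the current text: four unranked measures at three visits in the Abstract and Objectives, against abduction with no visit in the sample size section, under one unadjusted threshold. The false-positive chance is 46% for 12 independent tests, about 25-40% under the assumed correlations, and about 11-14% even if only abduction counts. Only a single measure at a single named visit gives 5%. The independent figures are arithmetic; the others rest on correlations that the documents do not supply.

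The sample size arithmetic is correct for what it computes. It supports one comparison of an abduction score, not four primaries and not abduction in degrees. The wording on time origin is a smaller matter: Objectives is the outlier, but the visit must be unambiguous once one is named.

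**What to change.** 1. In the Abstract's Objective, in Objectives and in the Primary Variable section, name the same single primary endpoint at one stated visit. Abduction is the natural choice because the sample size rests on it. The documents do not determine the visit. Day 32 carries the secondary objective of sustained 50% improvement, but that does not bar it for a comparison of means.
2. State the scale. If abduction is analysed in degrees, restate the sample size justification with a difference and SD in degrees. If the score is kept, define it.
3. Make VAS, SPADI, McGill, the other movements and the other visits secondary. Alternatively, keep several primaries with a prespecified multiplicity adjustment and restate the power.
4. In Statistical Methods, say which measure and visit the deciding ANOVA uses.
5. Align the visit wording in Objectives with the study-day count in the Overview and Table 6. Also settle whether baseline is day 0 (Table 6) or day 1 (Study Procedure).
6. Make and date the change as an amendment before any comparison by group, and state whether the analysis reported as in progress compared the groups.

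Cost: the other measures lose confirmatory status, and because recruitment began in October 2024 this is a mid-trial amendment to be declared. Naming one primary needs no extra visits. The number of patients stays at 60 only if the justification still holds on the chosen scale; keeping several primaries would raise it, or lower the power, as shown above.

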### Secondary Objective

The secondary objective is to evaluate and compare the sustained relief on the 32nd day in each group, defined as maintaining at least a 50% improvement in the VAS score, ROM, McGill Pain Questionnaire score, and SPADI score compared to baseline measurements.

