### Inclusion and Exclusion Criteria

This study will include (1) patients who are willing to provide written informed consent; (2) patients who are fit for nasal oil administration as per classic Ayurvedic guidelines [21] (ie, those who are free of indigestion; have not consumed food or alcohol recently; or do not have severe thirst, hunger, or exhaustion); (3) patients of either gender aged 20 to 60 years [22]; (4) patients with controlled type 2 diabetes mellitus (fasting blood sugar ≤140 mg/dL and postprandial blood sugar ≤180 mg/dL); and (5) patients with primary FS at the inflammatory (first) and frozen (second) stages. This study will exclude patients who are unfit for thermal cauterization [23]; patients who are contraindicated for physiotherapy (eg, those with epilepsy or a pacemaker); patients with trauma or injury (eg, dislocation or fracture of the shoulder and clavicle); patients with uncontrolled hypertension (160/100 mm Hg); patients who have rheumatoid arthritis, spinal canal stenosis, all types of malignancies, and stroke; patients with infectious conditions or systemic disorders; patients who are indicated for FS surgery; postoperative patients with FS; and pregnant and lactating women.

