#### Normal ROM of the Shoulder Joint

The goniometer measures the shoulder’s ROM before and after treatment [29].

Flexion, extension, abduction, adduction, and internal and external rotation are possible shoulder movements, and the normal readings for these movements are shown in Table 4.

**Table 4. T4:** The regular movements and readings for the shoulder joint.

Movement	Normal reading (degrees)
Flexion	180
Extension	50
Abduction	180
Adduction	50
Internal rotation	90
External rotation	90

All the ROM measurements will be taken in a standing position, and the participant will be instructed to place the back of the head, back and buttocks, and heels against the wall to prevent the trunk from moving. Each movement will be measured 3 times on a goniometer at the glenohumeral joint to avoid human error, and the average of 3 readings will be calculated and recorded.

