### Randomization and Allocation

Computer-generated random numbers will be used to create a randomization chart. The participants will be randomized at a ratio of 1:1:1. To guarantee that treatment assignments are balanced, allocation sequence creation will be conducted using permuted blocks and provided in a randomized table. The researcher will enroll and give the participants an intervention and allocation sequence.

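### Sustained relief applies a 50% improvement rule to ROM that, read on goniometer degrees, is out of reach above two thirds of normal and easily met by a very stiff shoulder

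*Protocol article*

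**What the plan says.** The Secondary Objective section of the protocol article defines sustained relief on day 32 as "defined as maintaining at least a 50% improvement in the VAS score, ROM, McGill Pain Questionnaire score, and SPADI score compared to baseline measurements". One threshold and one reference, the patient's own baseline, cover all four measures.

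The section on normal ROM gives the instrument, "The goniometer measures the shoulder’s ROM before and after treatment", and states that "the normal readings for these movements are shown in Table 4": 180 degrees for flexion and abduction, 90 for internal and external rotation, 50 for extension and adduction. The sample-size section describes improvement in abduction as "measured as the increase in the range of motion after the intervention".

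The eligibility criteria admit "patients with primary FS at the inflammatory (first) and frozen (second) stages" and state no minimum loss of ROM.

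The article nowhere expresses ROM improvement as a share of the lost range. It does not say which of the six movements count towards sustained relief, or whether a patient must meet all four measures together.

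**The concern.** A relative improvement of 50% means different things on scales that run in opposite directions. On VAS and SPADI zero is the best value, and the McGill result is a summed pain index on which lower is better. Halving such a score is possible from any nonzero baseline. ROM rises towards a normal reading, so the demand in degrees grows with baseline while the room to improve shrinks. The better the shoulder at entry, the harder the criterion, until it cannot be met. The worse the shoulder, the smaller the gain that counts.

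At stake is the meaning of the ROM responder proportion. It can rank a fully recovered shoulder below one that remains severely restricted, and so reflect baseline ROM as well as treatment effect.

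**Working it through.** **The plan's own figure.** No sample size is given for this endpoint. The one stated, for abduction improvement, reproduces: 2 × (1.96 + 0.84)² × 0.58² / 0.526² = 19.06, rounded up to 20 per group. It does not depend on the sustained-relief definition.

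**Inputs.** Threshold 50% over baseline (Secondary Objective); improvement as an increase in degrees (sample-size section and ROM section); normal readings N (Table 4); no ROM limit at entry (eligibility criteria); 20 patients per arm.

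**Reachability.** For baseline b, success on ROM needs a day 32 reading of at least 1.5 × b. Taking N as the ceiling, this is possible only if 1.5 × b ≤ N, that is b ≤ N/1.5, or two thirds of normal.

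- Flexion, abduction: 180/1.5 = 120 degrees
- Internal and external rotation: 90/1.5 = 60 degrees
- Extension, adduction: 50/1.5 = 33.3 degrees, passed by any patient who has lost less than 50 − 33.3 = 16.7 degrees

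**What the rule asks for abduction (N = 180).** Gain needed = 0.5 × b; share of deficit = 0.5 × b / (180 − b).

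| Baseline | Target | Gain needed | Share of deficit |
|---|---|---|---|
| 20 | 30 | 10 | 6% |
| 40 | 60 | 20 | 14% |
| 90 | 135 | 45 | 50% |
| 120 | 180 | 60 | 100% |
| 130 | 195 | 65 | 130% |
| 150 | 225 | 75 | 250% |

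**Two contrasting patients.** Abduction 130 to 180: (180 − 130)/130 = 38.5%, a failure, although the whole deficit is recovered. Rotation 10 to 15: (15 − 10)/10 = 50%, a success, with (15 − 10)/(90 − 10) = 6% of the deficit recovered and 75 degrees still missing.

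**Share of patients affected.** The documents give no baseline ROM distribution. As an assumption only, let baseline abduction be normal with mean 80 to 110 and SD 20 to 30 degrees. The share above 120 is 1 − Φ((120 − mean)/SD). It runs from 2% (mean 80, SD 20) to 37% (mean 110, SD 30).

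**Effect on a responder rate.** One patient in 20 is 1/20 = 5 percentage points, and two are 10. These are upper bounds, because a patient changes the rate only if a sound ROM criterion would have counted that patient as a success.

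**The case against.** The strongest reply is that the article does not write out a formula for ROM improvement, and that its only worked abduction figures are on a graded score where lower is better. That score falls from 2.23 to 1.06, with "Difference (pretest-posttest)=1.17", a fall of 1.17/2.23 = 52%. On such a score a 50% improvement has no ceiling problem. But nothing ties the score to sustained relief. The ROM outcome is specified as goniometer readings, and the same sample-size section describes improvement as an increase in range. The literal reading therefore stands, and an analysis plan that followed the stated rule would inherit the fault.

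Three stronger inferences are tempting, and the documents do not support them.

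- A reader might infer that a ROM failure fails the patient on the whole endpoint. The four measures are joined by a plain conjunction, and elsewhere the article lists them as separate criteria. Whether all must be met together is open. If so, the ROM rule alone would fail such a patient whatever the pain relief.
- A reader might infer that patients above two thirds of normal are being enrolled. Eligibility permits this but does not show it, and the Background section says that motion is significantly reduced in all directions in frozen shoulder. Few may be affected in the most restricted movements. The 33.3-degree limit could bind sooner.
- A reader might infer that chance imbalance in baseline ROM would drive the between-arm comparison. That needs an unknown prevalence, an imbalance, and patients who would otherwise have succeeded.

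Two further objections stand. The Table 4 value is a normal reading, and some people may exceed it. A rule based on the deficit also has a weak end: from a baseline of 170 degrees a gain of 0.5 × (180 − 170) = 5 degrees would suffice, and the ratio is undefined at a normal baseline. The fix must guard against both.

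**Conclusion.** The definition is wrong as written for ROM. On goniometer degrees it asks for more than the Table 4 normal above 120, 60 or 33.3 degrees, depending on the movement, and it accepts a recovery of about 6% of the deficit in a very stiff shoulder. This rests on reading improvement as a rise in degrees relative to baseline and on taking the Table 4 reading as the practical ceiling.

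The effect on the results cannot be sized from the documents beyond the bound of 5 percentage points per affected patient in an arm's ROM responder rate. The fault is confined to the secondary endpoint. The planned comparison of means by ANOVA or ANCOVA and the sample size do not use it. It should be fixed, but it does not undermine the primary analysis.

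**What to change.** Before results by arm are examined, redefine the ROM criterion as recovery of at least half the baseline deficit:

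(day 32 − baseline) / (Table 4 normal − baseline) ≥ 0.5

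Name one movement in advance; abduction is the natural example, since the sample-size section calls it the primary variable. Apply the criterion only to patients whose baseline deficit exceeds a pre-stated measurement-error margin, which removes the undefined ratio and the trivial gains near normal.

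For abduction the gain needed, (180 − b)/2, becomes 80 degrees from a baseline of 20, 45 from 90, 30 from 120 and 15 from 150. It is attainable at every baseline below normal. It agrees with the present rule only at b = 90, where 0.5 × b = (180 − b)/2. Abduction from 130 to 180 would then pass (50/50 = 100% of the deficit), and rotation from 10 to 15 would fail if rotation were the named movement.

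Keep the 50% reduction for VAS, SPADI and McGill. Report the proportion for each measure separately, alongside any composite, and state whether a composite requires all four.

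The criterion uses data already collected. The cost is a documented change to a secondary definition during recruitment: the Results section reports 16 participants by January 2025 and analysis in progress, so timing matters. Patients with near-normal baseline in the named movement would not contribute to the ROM proportion.
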